## Abstract

**Context:**

At least 40% of cancers are linked to environmental or behavioral factors, and dietary behavior appears to be a major lever. Epidaure Market is a prevention initiative developed using a method for co-constructing health promotion initiatives and prevention programs that stratifies evidence from the scientific literature and combines it with experiential knowledge (DEVA, TPB, BCT). It promotes a sustainable diet (i.e., healthy, ecological and ethical nutrition) among 5th and 4th grade students during the crucial period of adolescence, when these behaviors are often far from the recommendations.

**Method:**

The protocol implemented was carried out in 72 middle school classes in the Montpellier and Dijon academies. The intervention included teaching sessions and a virtual supermarket game, integrated into the school curriculum and delivered by science teachers. Effectiveness is tested in a cluster randomized controlled trial with 3 evaluation times (pre- and post-intervention and 1 follow-up). The study also includes an implementation assessment, with process analysis and implementation elements, as well as a transferability assessment based on key functions (FIC model and Astaire grid).

**Expected outcomes:**

The study is still underway within the school. The primary expected outcome is a positive influence on the motives underlying food choices to move towards a sustainable diet. Secondary expectations involve changes in variables such as self-efficacy and perceived social norms, as well as an increase in knowledge about healthy eating. We also expect the qualitative approaches to provide information on the deployment process in the new territories.

**Discussion:**

The study aims not only to demonstrate the effectiveness of Epidaure Market, but also to identify the optimal conditions for its nationwide implementation in France’s middle schools. Ultimately, the initiative aims to help reduce the incidence of cancer by promoting healthier eating habits among teenagers.

## 1. Introduction

Worldwide, unhealthy eating is an evitable risk factor in the development of non-transmissible diseases such as cardiovascular disease, cancer and type 2 diabetes [1]. In France, cancer then cardiovascular disease account for the highest number of deaths [2]. In the case of cancer, the number of new cases almost doubled between 1990 and 2023 [3]. Overweight/obesity and unbalanced diet are among the main risk factors for preventable cancers, just after tobacco and alcohol [3]. In France, 19,000 new cases were attributable to overweight in 2015, and only 28% of adults ate 5 fruits and vegetables a day [3]. As a result, promoting healthy eating at all ages is a global public health priority [4] and in France, a priority area of prevention with, in particular, the ten-year cancer control strategy 2021–2030 [5] and the National Nutritrion Sante Program (PNNS 4), which aims to improve health through nutrition for the French population [6].

In addition to consequences on human health, food intake and related behaviors lie at the heart of global challenges pertaining to environmental degradation [7]. The food system, comprising the food supply chains, the food environment and consumers’ behaviors, has been estimated that just over one third of total greenhouse-gas emissions (GHGEs) stem from different procedures linked to the global food system–from production to consumption [8]. At the consumer level, the wide adoption of sustainable diets has the potential to contribute to a reduction in GHGEs and favourable health outcomes [9] Shifting towards sustainable diets requires the alignment of public health objectives, which are commonly outlined in national dietary guidelines [10, 11] with the environmental dimension of sustainability [12, 13]. The nutrition recommendations in France integrate environmental with health sustainability through specific food groups, for example limiting the intake of red and processed meats, but also highlighting aspects of production, for example increasing the consumption of foods from organic agriculture [6]. Public health strategies for children and adolescents focus on reducing the burden of non-transmissible diseases by improving diet, as eating behaviors acquired in childhood persist into adulthood [4, 14] and are more complex to change later on [15]. Some studies show that young people eat too many unhealthy foods such as fast food and high-calorie foods [16] and eat too few fruits and vegetables [17, 18]. 23% of children aged 6–17 reached the consumption benchmark of at least 5 portions of fruit and vegetables a day, and 36% of children consumed at least 125 ml of sweetened beverages (i.e. half a glass) a day [19]. Adolescents may be more sensitive than adults to peer influence in terms of risk-taking, emotionality and health behaviors [15, 20–22], but other factors may also influence their food choices. Indeed, multiple interacting factors can influence adolescents’ food choices in a complex linking individual (e.g. psychosocial, biological and lifestyle), social and environmental (e.g. family and peers), social origins and associated resources (e.g. income, time and educational level have a strong influence on eating habits), physical environment (e.g. schools, fast food outlets and other stores) and societal system (e.g. media, marketing, culture and norms) factors [23–26].

For this reason, and in order to be effective, school-based interventions seem to be the ideal place, as this is where children and adolescents spend a large part of their day and are involved in a process of learning and behavior change [27, 28]. However, they must not focus solely on a knowledge-based approach [26]. Knowledge is necessary and is one of the determinants of food choice, but it contributes relatively little to changing dietary behavior [29]. A multi-component approach, included in the school program, teacher training and parent participation seems to be more effective [27, 28, 30].

Such multi-component interventions are even more effective when they are theory-based. Indeed, implementing and evaluating theory-based interventions is recognized as an effective means of improving health-promoting behaviors [31–33], by identifying key target constructs, and selecting appropriate intervention techniques [34]. Implementing theory-based interventions is for example effective for improving physical activity among adults [35], or reducing binge-drinking among adolescents [31]. However, in this latest review and meta-analysis, Gourlan and colleagues [31] highlight that the quality of theoretical implementation was globally low for most of the studies included, and that the reciprocal link between Behavior Change Techniques [BCT, 36] and conceptual constructs remained unclear. Concerning eating behaviors among young populations, a review of the literature [30] shows that multi-strategy interventions can be effective when nutrition education program is developed with theoretical models, combined to a facilitation of the programs by school staff and teachers, parental involvement, and changes to the school food environment.

Existing interventions generally focus on obesity prevention [37, 38] physical activity [26, 39] or the food environment [40]. There is no intervention on the motives of food choice, which is realized in middle school and theoretically grounded. Previous researches about dietary behaviors have indicated that food choice motives may play a mediating role between personal norms and values and dietary behaviors [41, 42]. Indeed some types of concerns (e.g.: health, environment, etc.) may be explained by a combination of values that seems to influence dietary behaviors such as purchases and food choices and thus diet quality [41]. Several studies have showed that sustainable food motives such as such as ethics and environment, local and traditional production and health are related to healthier dietary patterns, higher consumption to fruit and vegetables and lower consumption of high-fat high sugar food, notably in young individuals [43–46]. This intervention is based on a serious game simulating a virtual supermarket (www.epidauremarket.fr).

The “Epidaure Market” intervention has been developed with a multi-disciplinary team in the Epsylon laboratory of Montpellier, using a co-construction method for health promotion actions and prevention programs that allows to stratify evidence from the scientific literature, and combine these data to experiential knowledge [DEVA method, 47]. Selected final variables integrated, among others, constructs of the theory of planned behavior [TPB, 48], one of the most widely tested models of the factors influencing health-related behaviors [49]: self-efficacity, prescriptive and descriptive social norms, attitudes, awaiting results, skills in nutrition choices, knowledge of the environmental and health impact of nutrition, and of marketing strategies. Based on an online tool [50] linking behavior change techniques and mechanisms of action, theorical constructs and relevant factors were operationalized in appropriate BCT.

Population health interventions are inherently complex. Complexity-resulting from interactions among many components parts-is a property of both the intervention and the context (or system) for which it is developed [51]. Recently, Cambon and colleagues [52, 53] have proposed the use of the notion of *interventional system* rather than intervention, in order to better take into account the interaction of contextual elements in producing the effects of an intervention. The "interventional system" is defined by the authors as: a set of interdependent human and non-human contextual agents within spatial and temporal boundaries, generating mechanistic configurations—mechanisms—that are preconditions for change in health. Process evaluations are recommended to open the "black box" of interventions in trials [54] and are considered essential for complex interventions, i.e. interventions with many potential active ingredients that are often difficult to implement [55]. As Epidaure Market is a complex intervention, a process evaluation was incorporated into the cluster randomized controlled trial.

Thus, when an intervention deployed in one context (geographical, socio-cultural, etc.) is reproduced in another context, territory, a central question concerns the conditions of its transferability. Transferability is understood as the extent to which the measured effectiveness of an applicable intervention could be achieved in another setting [56]. Transferability criteria take into account elements that belong to the intervention itself (its components and implementation conditions), but also elements from the context that can influence not only this implementation, but also the results more directly. These elements are the characteristics of the populations, the stakeholders and the context in which the intervention is implemented. Thus, the notion of transferability fully integrates that of the intervention system, in that it gives an important contribution to the effect due to the context. The main challenges of transferability studies are to increase the public health impact of an intervention evaluated as effective, by reproducing it in another context, while managing to reduce (or at least not worsen) social inequalities in health [57].

The present study describes the research protocol for a randomized controlled trial evaluating the efficacy of the intervention “Epidaure Market”, and a qualitative study evaluating its implementation and transferability. This school-based action aimed at (i) improving food choices among middle school students by acting on their motives in favor of a sustainable diet, (ii) theoretically anchored on behavior change techniques drawn from BCT, (iii) and aimed at an audience enabling the intervention to be included in the school curriculum and offered by science teachers, while involving parents with home-based work.

## 2. Method and analysis

### 2.1 Study objective and endpoints

The primary objective of the efficacy study is to assess whether the intervention influences food choice motives towards a sustainable (healthy, ecological and ethical) diet. Secondary objective will assess whether the intervention improves self-efficacy in food choices, influences social attitudes and perceptions towards food, and improves skills and knowledge in nutrition, marketing strategies and the environmental impact of food. The applicability and conditions of transferability will be assessed, in two different areas due to their disparities (Montpellier and Dijon School Academies). Hérault and Gard departments are located in the Occitanie region, a region with strong demographic growth. Whereas Nièvre, Côte d’Or and Sâone-et-Loire, Yonne departments, located in the Bourgogne-Franche-Comté region, are the 1^re^ rural region in France ahead of Bretagne with its 4 departments.

### 2.2 Study design

Epidaure Market is a multicenter, two-arm (allocation ratio 1:1), cluster randomized controlled trial. The protocol is registered with ISRCTN registry (ISRCTN15372343). The intervention took place over three classroom sessions, organized by science teachers. Measurements are taken by the research team in both territories: before the first intervention session (T0); post-intervention (T1), one month after the end of the sessions; and a follow-up (T2), four to six months later (see Fig 1).

**Fig 1 pone.0306781.g001:**
[figure not shown]
Flowchart of the Epidaure Market cluster randomized controlled trial.

At the same time, a process and implementation evaluation as well as a transferability analysis are carried out. The process and implementation evaluation is based on student focus groups and semi-structured interviews with teachers, parents and school management staff and the Rectorate. Transferability is assessed using the Astaire and FIC tools. This more qualitative study was carried out after the Epidaure Market intervention.

### 2.3 Number of subjects required

The primary outcome is defined as the proportion of students who improve their motivation to healthy sustainable food choices. By assuming a proportion of 5% in the control group (due to slight variation, independent of intervention), a type I error at 5% and a variation coefficient of cluster size of 50% (because class sizes can vary between 20 and 30), 36 clusters with 25 subjects in each group (control and intervention) allow to achieve 90% power to detect a difference between 5.0% and 11.5% in the proportion of students who improve their motivation to choose good food, by varying the intra-cluster correlation between 0.02 and 0.2. A 10% attrition effect was allowed for. To compensate for this loss, more classes were recruited for each area.

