### 2.4 Participants and recruitment

The design of the efficacy study is a cluster-controlled randomized trial to compare an intervention group (n = 36 classes in which the intervention is carried out) and a control group (n = 36 classes without intervention). These 72 second and third year junior secondary school classes are distributed as follows: 40 in Montpellier and 32 in Dijon. The population consists students aged between 12 and 14 years. In Occitanie, only secondary schools in the Gard and Herault departments took part in the study. Herault has 81 public secondary schools and 29 private secondary schools under contract, i.e. 110 establishments. Gard has 69 public secondary schools and 29 private secondary schools under contract, for a total of 98 establishments. At the start of the 2022 academic year, the Dijon academy (4 departments) have 158 public secondary schools and 24 private secondary schools under contract, for a total of 182 establishments. Secondary schools in the Nièvre, Côte d’Or and Soâne et Loire departments are those taking part in Epidaure Market. The last department could not be represented. To this end, all schools will be geolocated using their exact address, in order to identify the IRIS (Ilots Regroupés pour l’Information Statistique [grouped plots for statistical information]) to which they are attached. The IRIS is the basic unit for the dissemination of sub-municipal statistics, and represents a partition of the territory of these communes into "neighborhoods" with a population of around 2,000 inhabitants. The level of deprivation of the IRIS will then be assigned using the French European Deprivation Index (F-EDI) [58]. Due to school mapping, we assume that the IRIS deprivation level of the schools reflects the deprivation level of the children’s living areas, which is also assessed at the individual level. This approach has already been used in studies of the European adolescent health survey HBSC, Health Behaviour in School-Aged Children [59].

Participants for the Epidaure Market must (i) be students aged between 12 and 14 years, (ii) 5th and 4th grades, (iii) whose parents have agreed to answer the questionnaires, (iv) and have the student’s consent.

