## 4. Results

Recruitment began in September 2022 and will run until June 30, 2024. The 72 classes recruited will be followed over two school years. Different classes were recruited between the 2022–2023 and 2023–2024 school years.

Focus groups and qualitative interviews began in January 2024 and will continue until the end of June 2024

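### Section 2.3 says extra classes were recruited to cover 10% attrition, but the 36 classes per arm reported are the number that gives the stated power with no attrition

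*Protocol article*

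**What the plan says.** Section 2.3 sets out the sample size. The inputs are a control proportion ("By assuming a proportion of 5% in the control group"), "a type I error at 5"%, a class-size term ("a variation coefficient of cluster size of 50% (because class sizes can vary between 20 and 30") and an intra-cluster correlation (ICC) from 0.02 to 0.2. The result is that "36 clusters with 25 subjects in each group (control and intervention) allow to achieve 90% power" for differences from 5.0 to 11.5 points. The section then says that 10% attrition was allowed for, and adds: "To compensate for this loss, more classes were recruited for each area". It does not say how many classes were added, or from what base.

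Section 2.4 describes the trial as "an intervention group (n = 36 classes in which the intervention is carried out) and a control group (n = 36 classes without intervention"), and places 40 classes in Montpellier and 32 in Dijon, which is 72. Section 4 states: "The 72 classes recruited will be followed over two school years". The Abstract also gives 72 classes. The 36 and 36 split appears in section 2.4 only.

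**The concern.** If 36 per arm is what the calculation needs, and more classes were then recruited to cover losses, the trial should have more than 36 per arm. If instead 36 already contains the allowance, the calculation should return the published range at about 90% of that size. The article gives one number for both the requirement and the recruited total. A reader is told that the design is protected against 10% loss, and the published counts contain no visible protection. At stake is whether the stated 90% power and the detectable differences describe the trial after attrition or only a trial that loses nobody.

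**Working it through.** **Inputs (section 2.3).** Control proportion p1 = 0.05; type I error 5%, taken as two-sided because sidedness is not stated; k = 36 classes per arm; m = 25; CV of class size 0.5; ICC ρ = 0.02 and 0.2; attrition 10%. The figures 5.0% and 11.5% are read as the range of detectable differences. Read as 5% versus 11.5%, power at 36 × 25 would run from about 98% (ICC 0.02) to 54% (ICC 0.2), which does not match the stated 90%.

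**Formulas.**
- L = mρ / [1 + (m − 1)ρ]
- Design effect DE = [1 + (m − 1)ρ] / [1 − CV²·L(1 − L)]
- Effective number per arm n_eff = k·m / DE
- Required n per arm = [1.96·√(2p̄(1 − p̄)) + 1.2816·√(p1(1 − p1) + p2(1 − p2))]² / (p2 − p1)², with p̄ the mean of p1 and p2

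**Step 1: reproduce the plan's figure, 36 × 25, no loss.**
- ICC 0.02: 1 + 24 × 0.02 = 1.48; L = 0.5/1.48 = 0.338; DE = 1.48/(1 − 0.25 × 0.224) = 1.568; n_eff = 900/1.568 = 574; detectable difference 5.04 points.
- ICC 0.2: 1 + 24 × 0.2 = 5.80; L = 5/5.8 = 0.862; DE = 5.80/(1 − 0.25 × 0.119) = 5.978; n_eff = 900/5.978 = 151; detectable difference 11.49 points.

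Both match the published 5.0 and 11.5. Power for exactly those differences is 89.7% and 90.0%. So 36 classes of a full 25 is the requirement before any loss.

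**Step 2: apply 10% loss, and compare with an inflated design (CV 0.5).** Each pair is ICC 0.02, then ICC 0.2. Power is for 5.0 and 11.5 points respectively.

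| Classes × pupils per arm | DE | n_eff | Detectable difference (points) | Power |
|---|---|---|---|---|
| 36 × 25 (no loss) | 1.568; 5.978 | 574; 151 | 5.04; 11.49 | 89.7%; 90.0% |
| 36 × 22.5 (10% of pupils lost) | 1.511; 5.475 | 536; 148 | 5.24; 11.62 | 87.5%; 89.5% |
| 32.4 × 25 (10% of classes lost) | 1.568; 5.978 | 517; 136 | 5.36; 12.30 | 86.3%; 86.8% |
| 40 × 22.5 (inflated, pupils lost) | 1.511; 5.475 | 595; 164 | not needed | 90.7%; 92.4% |

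Of the three 36-class scenarios, only the loss-free one returns the published range.

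**Step 3: the allowance.** 36/0.9 = 40 classes per arm, 80 in total, against 72 reported. The 40 in section 2.4 is something else: it is the Montpellier total over both arms.

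**Step 4: the CV.** With a mean of 25, class sizes of 20 to 30 have a standard deviation of at most 5, so the CV is at most 5/25 = 0.20. If sizes are uniform it is (10/√12)/25 = 0.12. At CV 0.20, 36 × 22.5 gives DE 1.442 and 5.327, n_eff 562 and 152, detectable differences 5.10 and 11.42 points, and power 89.0% and 90.3%. At CV 0.12, power is 89.2% and 90.4%.

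**The case against.** **The 36 may already include the allowance.** With the plan's own CV this fails, because neither 36 × 22.5 nor 32.4 × 25 gives 5.0 and 11.5. An equal-cluster formula with 22.5 pupils comes close (5.08 and 11.38 points), but it discards the CV that section 2.3 says was used. Even on that reading no extra classes appear in the article.

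**The stated CV is too large for the stated class sizes, and that slack roughly absorbs pupil loss.** This stands. With a CV of 0.20 or less, 36 classes of 22.5 keep about 89 to 90% power. A reader might infer that the trial is materially underpowered, and the documents do not support that.

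**A more conservative design effect makes things look worse.** The form 1 + ((1 + CV²)m − 1)ρ gives 84.3% power at ICC 0.2 after 10% pupil loss, and a reader might blame attrition. The same formula gives 84.7% with no loss, so attrition accounts for 0.4 points. It also yields 12.8 points at ICC 0.2 with no loss, so it is not the formula that reproduces the plan.

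**The recruitment sentence may be true.** It reports a past event by area, section 4 has recruitment open until 30 June 2024, and the flowchart is not shown. A reader might infer that the sentence is false. The article shows only that it and the class counts cannot both be right as written.

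**Twenty-five need not mean full participation.** It is the mid-point of 20 to 30, and entry depends on parental agreement and pupil consent. That the calculation assumes whole classes taking part is an inference, and the point does not depend on it.

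**An article condenses the full protocol.** That excuses an omission. It does not excuse a positive statement that conflicts with counts in the same article.

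**Conclusion.** The point holds as an internal inconsistency with a small numerical effect. Section 2.3 claims a class-level reserve that the reported counts do not contain, and the stated 90% power belongs to a trial with no loss. On the plan's CV of 50%, 10% pupil loss costs about 2.2 power points at ICC 0.02 and 0.5 at ICC 0.2. Loss of 10% of whole classes costs about 3 points. If the CV is at most 0.20, pupil-level loss leaves power at about 89 to 90%.

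This rests on a two-sided 5% test, on the design effect that reproduces both published differences, and on a CV that is unchanged by attrition. Section 2.3 does not say whether the 10% refers to pupils or to classes, so both are shown. The ICC range alone moves the detectable difference from 5.0 to 11.5 points, far more than attrition does. The text should be corrected, but nothing here calls for more classes.

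**What to change.** Establish first how many classes were randomised, then make sections 2.3, 2.4 and 4 and the Abstract agree. State the number of classes per arm before and after the allowance, and whether the 10% is loss of pupils or of classes.

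- If 72 is the number randomised: remove the claim of compensation and give power or detectable difference net of attrition. On the stated CV of 50%, that is 5.2 to 11.6 points for pupil loss (power 87.5% and 89.5% for the stated differences), or 5.4 to 12.3 points for loss of whole classes (about 86 to 87%).
- If more than 72 were randomised: correct 72 and 36 wherever they appear and recompute.

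In the same edit, reconcile the CV of 50% with class sizes of 20 to 30. If the CV is brought down to 0.20 or less, the net range for pupil loss is 5.1 to 11.4 points.

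The cost is a sentence or two and, in the first case, a slightly less favourable stated figure. No extra classes are needed.
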